# PATCH: posture and mobility training for care staff versus usual care in care homes: study protocol for a randomised controlled trial

**DOI:** 10.1186/s13063-018-2863-5

**Published:** 2018-09-24

**Keywords:** Care homes, Nursing homes, Older people, Feasibility, Cluster randomised controlled trial, Staff training, Physiotherapy, Posture, Mobility, Process evaluation

## Abstract

**Background:**

Residents of care homes have high levels of disability and poor mobility, but the promotion of health and wellbeing within care homes is poorly realised. Residents spend the majority of their time sedentary which leads to increased dependency and, coupled with poor postural management, can have many adverse outcomes including pressure sores, pain and reduced social interaction. The intervention being tested in this project (the Skilful Care Training Package) aims to increase the awareness and skills of care staff in relation to poor posture in the older, less mobile adult and highlight the benefits of activity, and how to skilfully assist activity, in this group to enable mobility and reduce falls risk. Feasibility work will be undertaken to inform the design of a definitive cluster randomised controlled trial.

**Methods:**

This is a cluster randomised controlled feasibility trial, aiming to recruit at least 12–15 residents at each of 10 care homes across Yorkshire. Care homes will be randomly allocated on a 1:1 basis to receive either the Skilful Care Training Package alongside usual care or to continue to provide usual care alone. Assessments will be undertaken by blinded researchers with participating residents at baseline (before care home randomisation) and at three and six months post randomisation. Data relating to changes in physical activity, mobility, posture, mood and quality of life will be collected. Data at the level of the home will also be collected and will include staff experience of care and changes in the numbers and types of adverse events residents experience (for example, hospital admissions, falls). Details of NHS service usage will be collected to inform the economic analysis. An embedded process evaluation will explore intervention delivery and its acceptability to staff and residents.

**Discussion:**

Participant uptake, engagement and retention are key feasibility outcomes. Exploration of barriers and facilitators to intervention delivery will inform intervention optimisation. Study results will inform progression to a definitive trial and add to the body of evidence for good practice in care home research.

**Trial registration:**

ISRCTN Registry, ISRCTN50080330. Registered on 27 March 2017.

**Electronic supplementary material:**

The online version of this article (10.1186/s13063-018-2863-5) contains supplementary material, which is available to authorized users.

## Background

Life expectancy has increased dramatically over the last century. As the population ages, the numbers at the oldest ages will increase the fastest. In mid-2016, there were 1.6 million people aged 85 years and over; by mid-2041, this is projected to double to 3.2 million [1]. One consequence is an increase in the demand for long-term care which, despite the increased emphasis on community care [2], will remain a necessary component of health and social care provision [3]. The need for care home places is predicted to rise by 150% in the next 50 years [4]. Increasing age is associated with increasing disability. A United Kingdom (UK) survey [5] reported that 89% of residents of care homes required care because of disability from long-term conditions, 72% had mobility problems and 62% were confused.

Residents of care homes are among the frailest in our population with significant health and social care needs [6]. The health requirements of residents place considerable burden on the UK National Health Service (NHS) and greater demands are placed on the workload of general practitioners (GPs) providing care for care home residents than caring for people in their own homes [7]. Care home residents are significantly more likely to attend emergency departments by ambulance and be admitted to hospital compared to the older population generally [8]. Hospital admission exposes residents to the risk of nosocomial infections and falls, and is disruptive for this frail population as they struggle to return to their previous health state once discharged.

The promotion of the health of frail older people in care homes is poorly and inconsistently developed. Provision of programmes which could promote health and wellbeing within UK nursing homes is only patchily realised [9]. A 2001 survey showed that only 10% of care home residents receive physiotherapy and just 3% occupational therapy [10]. It is reported that care home residents spend the majority of their time inactive [11–13] with low levels of interaction with staff. Previous work by members of this team [14] indicated that residents spent up to 13 h of their waking day sedentary. Sedentary behaviour is adversely associated with chronic disease risk factors and all-cause mortality [11]. Decreasing mobility, increasing dependency and poor postural management have many adverse effects. For residents in care homes, this may lead to increased incidence of pressure sores, pain, contractures and loss of independence [15], reducing opportunities to participate in social activities. Social isolation negatively impacts on mood and self-esteem, which can then further adversely affect physical health [16].

A Cochrane Review of rehabilitation in long-term care [17] reported that it was possible to improve physical activity in this population but that interventions were often time-limited and resource-intensive. A potentially more sustainable approach is to enhance the culture in care homes. To address this, a group of senior physiotherapists developed and piloted a manualised, competency-based training programme focused on posture and mobility called the Skilful Care Training Package (SCTP), which showed initial promise in raising awareness and providing practical skills training to staff in early pilot work. This paper describes the protocol for the feasibility trial evaluation of the SCTP compared with usual care (UC), within care homes.

## Methods / design

### Design summary

The PATCH trial is a multicentre, two-arm, pragmatic, cluster randomised controlled feasibility trial. A summary of the trial design is illustrated in Fig. 1.

**Fig. 1 Fig1:**
[figure not shown]
SPIRIT figure. *Further detail is provided in Table 1

### Aims and objectives

The aim of this trial is to assess the feasibility of conducting, and to inform the design of, a definitive randomised controlled trial (RCT) to investigate the clinical and cost-effectiveness of the SCTP compared with UC, within care homes. Figure 2 illustrates trial processes from screening to follow-up.

**Fig. 2 Fig2:**
[figure not shown]
Trial flow diagram

The objectives are to:Ascertain recruitment and retention rates at the level of the care home, staff and residents.Assess feasibility and acceptability of follow-up (retention of participants and completeness of data).Assess the appropriateness of outcome measures to inform the choice of primary and secondary outcomes for the main trial.Explore and clarify procedures to collect anonymised data at the level of the home.Assess the feasibility and best methods of collecting resource and outcome data for a future large-scale cost-effectiveness analysis. This will also involve exploration of the reliability of routinely collected NHS and care home data.Monitor relevant adverse events (AEs) and confirm how best to collect these.Assess the feasibility of delivering the SCTP.Develop methods to assess compliance with and adherence to the SCTP.Gain understanding of the barriers and enablers to delivering and implementing the SCTP in care homes to optimise implementation in the main trial.Obtain understanding of care home staff and trainers’ views of the SCTP to inform refinement for the main trial.Obtain insight from residents as to the acceptability of the SCTP to inform refinement for the main trial.Assess evidence of proof of concept relating to potential efficacy.Ascertain the number of care homes and residents needed for a definitive trial.Estimate the intra-class correlation coefficient (ICC) for the selected primary outcome from the trial data and from other literature and data sources.

### Recruitment setting

Ten residential and/or nursing care homes with residents aged 65 years or older in the counties of West and North Yorkshire in the UK will participate. These locations were selected to fit logistically with intervention delivery and research data collection. This geographical area covers a range of multi-ethnic rural and urban populations, so ensuring generalisability of findings. All care homes within these counties will be identified from the Care Quality Commission (CQC) care directory (accessed via www.cqc.org.uk). They will be approached if they have no more than four improvements on their latest CQC inspection report and no inadequate ratings. First contact with homes will involve sending a study flyer and summary information sheet to care home managers and following this up with a telephone call where no response is received. In addition to this ‘mail shot’ approach, the trial will be publicised at suitable local forums for care home managers and organisations and also by word of mouth by the trial team when they have opportunistic contact with care homes. An initial eligibility check will be undertaken over the telephone with managers at interested homes. If this check is positive, it will be followed by a visit to establish full eligibility and discuss trial procedures.

These recruitment processes will continue until 10 homes have been identified.

### Care home eligibility

Care homes (as defined above) will be eligible to take part if they meet all the following inclusion criteria:The manager has been in post for at least six months and is likely to remain in post for the study period.The manager is willing and able to release staff to attend SCTP training sessions and to contribute to data collection.Training in manual handling is provided to all direct care staff (a prerequisite for the SCTP training).It is anticipated that 12–15 eligible residents could be recruited to take part in the trial.

Care homes are not eligible to take part if they meet any of the following exclusion criteria:Is unsuitable for inclusion due to being subject to CQC improvements in areas relevant to the trial, enforcement notices / inadequate ratings, admissions ban, or relevant moderate or major compliance breaches.Is receiving special support for specific quality concerns (e.g. serious safeguarding investigations, voluntary or compulsory admissions bans).Physiotherapy training which involved postural management and physical activity has been delivered to staff in the last 12 months.The SCTP has already been delivered to the home.Is taking part in another trial or initiative which would conflict with the SCTP and / or with data collection required for this trial.

In larger homes, a particular unit (e.g. nursing unit) and the associated pool of staff may take part, rather than the whole home.

### Resident eligibility

Following care home agreement to participate, all residents will be screened for eligibility (anonymously to the trial team). Researchers will discuss resident eligibility with care home staff who will identify those who meet the inclusion criteria and record reasons for ineligibility.

All residents within the home (or participating unit) will be exposed to the intervention, should the home be allocated the SCTP; thus all may potentially benefit from enhanced staff knowledge and skills. Residents who are more likely to benefit from staff skills acquired during SCTP training, and where there are no confounding factors present that may affect outcomes, will be identified. Thus residents who are aged 65 years or older and are permanent residents within the home will be considered for participation in the data collection element of the trial, whereas those who are independently mobile (a Functional Ambulatory Classification [FAC] [18] score of 5 or 6), or who are currently having a course of physiotherapy, occupational therapy or speech and language therapy, or who have a life expectancy of less than three months will not be eligible to take part. It is anticipated that, should the intervention be effective, it would benefit residents regardless of mental capacity. Excluding those lacking capacity would affect the generalisability of the trial results and thus all eligible residents (with and without capacity) will be approached in line with the provisions of the Mental Capacity Act (MCA) [19].

### Resident recruitment and consent

The home manager or senior staff member will undertake an initial assessment of the capacity of each eligible resident to consent to take part in the trial. All residents will be assumed to have capacity to consent unless assessed to lack capacity in accordance with MCA guidance.

Where residents have capacity, care home staff will introduce the trial concept to them. If they are willing to consider involvement and agree to speak to the researcher, the researcher will discuss the trial in more detail and provide information about the study. Residents will be offered at least 24 h to consider involvement and consult with relatives, friends or staff if they wish. Thereafter, if they are still interested in participating, the researcher will obtain their written consent.

Where residents lack capacity, consultees will be identified and approached in line with procedures outlined in the MCA. Care home staff will identify a relative or friend who knows each resident well to approach to act as a personal consultee. The care home manager will send a study letter and information sheets to identified personal consultees, who will be given 10 days to respond before being sent a reminder letter and a further seven days to reply. They will be offered the opportunity to discuss the study with the researcher. Where a personal consultee does not respond or is unwilling to take on the role, a nominated consultee within the care home will be identified to provide their opinion on the resident’s wishes regarding study participation. Nominated consultees should be independent of the research, but in a care home setting this is difficult. As agreed with the Research Ethics Committee (REC), nominated consultees must not provide data about residents to maintain a level of independence from research procedures and should not, wherever possible, be directly involved in the resident’s care.

Capacity will be monitored on an ongoing basis, as will the availability of personal consultees. Any loss of capacity or changes in consultee would result in seeking a new consultee to facilitate continued participation.

### Staff involvement

Active involvement of care home staff is crucial to the trial. All nursing and care staff will be invited to take part in the study at each time point, with the exception of bank or agency staff who have worked in the home for less than one month during the preceding six months.

All eligible staff will be asked to provide data about themselves and their role, with some also asked to provide data about participating residents. If the care home receives the intervention, staff will be asked to attend training and will be invited to participate in the process evaluation interviews.

Staff members will be given a study information sheet before baseline data collection and again before each follow-up time point to ensure all currently employed care and nursing staff are aware of trial processes. Staff involved in specific roles (e.g. providing data about a resident) will be provided with a short supplementary information sheet about their role at the time of taking it on.

### Care home randomisation

Following confirmation of eligibility and consent (or consultee agreement), and subsequent to baseline assessments with/about participating residents, at the level of the home and from individual staff members, care homes will be randomised on a 1:1 basis to receive SCTP or UC. Randomisation will be performed by the statistical team at the Clinical Trials Research Unit (CTRU), using block randomisation with randomly selected block sizes. Concealment of sequencing is ensured by the physically separate locations of the CTRU and the blinded study researchers.

Following randomisation, the CTRU statistical team will inform the unblinded members of the research team of the randomisation outcome, so that arrangements for training in the intervention can be made for those homes allocated SCTP. Unblinded members of the research team will be informed of the random allocation of the last two homes at the same time, to avoid predictability of care home allocation and selection bias in the recruitment of homes and/or residents. An unblinded member of the research team will inform the care home manager of the treatment allocation by telephone and email. This same member of the team will arrange follow-up visits with managers in an effort to keep researchers undertaking outcome assessment blind to allocation throughout the trial. This will ensure researcher follow-up visits are not arranged at the same time as intervention training sessions within the home and will allow reinforcement of the need to not divulge allocation details.

To ensure sufficient outcome data for evaluation at six months, despite initial assessment that there should be 12–15 eligible residents at a participating care home, a minimum of eight participating residents will be accepted for homes to proceed to randomisation.

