### Intervention

The SCTP is a competency-based, manualised training programme which evolved through review of the evidence, needs analysis and expressed requirements of care home staff.

The training course aims to increase the skills of care assistants and nursing staff in handling techniques (to facilitate movement) and to promote good positioning (to maintain functional posture) thus protecting body shape, avoiding choking, reducing pain and encouraging activity, so enabling residents to be as active and independent as they wish to be. The course is designed to be delivered to all those providing care (care assistants and nursing staff) rather than to be cascaded down to staff via the training of key workers. The course is practical in nature and emphasis is given to person centred care and the development of empathy towards residents.

SCTP will be delivered by expert physiotherapists (trainers) to staff in each of the five care homes randomised to the intervention arm. Two trainers are co-applicants who have developed the SCTP, and all four trainers are qualified physiotherapists who each have recognised training qualifications. Together they have optimised the training package for use within the trial and have undertaken detailed training and development work to ensure quality and consistency of delivery.

Course content is manualised to ensure consistency, but the emphasis will be adapted according to the particular needs of a home and individual staff members. This will be done in consultation with the care home management team after randomisation and before the first training session. The SCTP is generally presented in three 2.5-h sessions with a ratio of one trainer to a maximum of eight staff, but can be presented over two or one longer session(s) if this fits better with staff availability and training plans.

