### Data collection

As the intervention will be delivered at the whole home level, it is important to assess the impact on the whole home. Thus data will be collected at the home level and from all care and nursing staff, as well as from and about participating residents. Data will be collected at baseline (before randomisation) and at three and six months post randomisation by blinded trial researchers who will visit each home at each time point. Maintenance of blinding will be monitored and reported by researchers as soon as they become aware of a care home’s allocation.

Personal details of participating residents will be held centrally, in accordance with the terms of consent or consultee agreement, to facilitate contact at follow-up time points. They will be held separately (both paper and electronic copies) to all outcome data.

A summary of assessments and outcome measures can be found in Table 1.

**Table 1 Tab1:** Summary and timing of assessments

Assessment	Method of completion	Timeline			
		Screening	Baseline	3 months	6 months
Screening, eligibility and consent					
Care home screening and eligibility	Researcher assessment / Researcher Interview (M)	X			
Resident screening and eligibility	Staff assessment with researcher support (S)	X			
Anonymous resident data: Physical Activity and Mobility in Residential Care Scale (PAM-RC) and Functional Ambulatory Classification (FAC)	Staff assessment with researcher support (S)	X		X	X
Trial consent (including process evaluation) (Resident (incl. personal/nominated consultee))	Self-completion (R) or Consultee (S, RF)		X		
Contact details (Resident (incl. personal/nominated consultee), staff informant	Researcher assessment (R, S, SI, RF)		X	(X)	(X)
Process evaluation consent	Self-completion (S)			X	X
Care home level data					
Care home demographics (including staff profile and training)	Researcher interview (M)		X	X	X
Home level resident profile	Researcher interview (M)		X	X	X
Significant events (D&V, temporary closure, CQC findings, change of manager/owner) and staff welfare	Researcher interview with manager / delegate (M)			X	X
Adverse events: total no. resident falls, hospitalisations and deaths	Researcher telephone interview with manager / delegate (M)		Collected monthly		
Staff measures (about the member of staff)					
Demographics	Self-completion (S)		X	X	X
Posture and movement questionnaire	Self-completion (S)		X	X	X
Kiersma-Chen Empathy Scale	Self-completion (S)		X	X	X

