#### Process evaluation

A mixed method approach will be adopted to explore the delivery and implementation of the SCTP.

Data regarding attendance, engagement, content and delivery of the SCTP will be provided by the trainers after every session in each of the five SCTP homes. This will be recorded on trial proformas which will allow reporting of adherence to the training content and schedule, as well as providing a summary of the level of staff understanding and engagement from the trainers’ perspective. Trainers will also have the opportunity to document any successes or difficulties, as well as deviations from the training plan, to allow for real-time reflection.

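### Releasing the last two allocations together conceals them only if the first eight homes split 4:4; after a 5:3 split, a five-per-arm total gives both away before those homes are randomised

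*Protocol article*

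**What the plan says.** All statements are in the protocol article.

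- **Number of homes.** Under Recruitment setting: "These recruitment processes will continue until 10 homes have been identified".
- **Method.** Under Care home randomisation, "care homes will be randomised on a 1:1 basis to receive SCTP or UC", and the CTRU statistical team does this "using block randomisation with randomly selected block sizes". The sizes are not given. Each home is randomised after its residents' consent and baseline assessments.
- **Arm size.** The Intervention section has the training delivered to "staff in each of the five care homes randomised to the intervention arm". The Process evaluation section has trainers report on sessions "in each of the five SCTP homes".
- **Disclosure.** After randomisation, "the CTRU statistical team will inform the unblinded members of the research team of the randomisation outcome", so that training can be arranged.
- **Safeguard.** The exception is the final pair: unblinded members are to be "informed of the random allocation of the last two homes at the same time, to avoid predictability of care home allocation and selection bias". The sentence goes on to name the recruitment of homes and of residents as what is being protected.

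**The concern.** The safeguard deals with one route to prediction. If the ninth allocation were disclosed alone, a five-per-arm total would reveal the tenth; holding both back closes that route. It does not close the route through the first eight allocations, which the unblinded team already has. If one arm already has five homes, the other must take both remaining homes, whether or not the two are released together. Random block sizes do not prevent this, because the observer needs only the total and the tally. Nor does the separation of the CTRU from the blinded researchers, because the inference comes from allocations already disclosed.

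Homes, participating units in larger homes, and residents are all chosen before a home is randomised, so foreknowledge at that stage could allow selection by arm. The two homes are 2/10 = 20% of the clusters. In the 5:3 case both fall in the same arm, so they are 2/5 = 40% of that arm's clusters in the cluster-level t-test on the PAM-RC and in the comparison of follow-up between arms.

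**Working it through.** **Inputs.** 10 homes, 1:1 allocation, five SCTP homes, permuted blocks of random size (all from the article). Block sizes are an assumption; I use equal-probability draws from {2, 4}, {2, 4, 6} and {4, 6}.

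**Step 1: the plan's own figure.** 10 homes at 1:1 gives 10/2 = 5 per arm, which agrees with the five SCTP homes stated.

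**Step 2: what is left after eight disclosures, total closed at 5:5.**

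- Split 4:4: places left are 5 − 4 = 1 and 5 − 4 = 1. The order is unknown, and joint release works.
- Split 5:3: places left are 5 − 5 = 0 and 5 − 3 = 2. Both homes go to the smaller arm with probability 1.

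So a 5:3 split after eight is the same event as homes 9 and 10 being in the same arm.

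**Step 3: chance of that event, blocks closing at 10.** If the final block has size b, the chance that its last two places are in the same arm is (b/2 − 1)/(b − 1): 0 for b = 2, 1/3 for b = 4, 2/5 for b = 6. The chance of each final block size follows from listing the block sequences that sum to 10, weighted by their draw probabilities.

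| Block sizes | Final block 2 / 4 / 6 | P(5:3 after eight) |
|---|---|---|
| 2 only | 1 / 0 / 0 | 0 |
| 2, 4 | 11/21 / 10/21 / 0 | 10/21 × 1/3 = 15.9% |
| 2, 4, 6 | 37/121 / 48/121 / 36/121 | 48/121 × 1/3 + 36/121 × 2/5 = 25.1% |
| 4, 6 | 0 / 1/2 / 1/2 | 1/2 × 1/3 + 1/2 × 2/5 = 36.7% |

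Exact enumeration of all sequences gives the same values.

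**Step 4: if the list is only cut off at 10.** Blocks may then run past the tenth home and 5:5 is not guaranteed.

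| Block sizes | P(5:3 after eight) | P(5:5 finish given 5:3) |
|---|---|---|
| 2, 4 | 10.4% | 100% |
| 2, 4, 6 | 20.4% | 80.6% |
| 4, 6 | 28.3% | 82.4% |

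For example, with sizes 4 and 6 the pairs 4-4, 4-6, 6-4 and 6-6 each have probability 1/4. P(5:3) = (0 + 2/5 + 1/3 + 2/5)/4 = 28.3%. The 6-6 case finishes 5:5 only half the time after a 5:3 split, so P(5:5 given 5:3) = (2/5 + 1/3 + 1/5)/(2/5 + 1/3 + 2/5) = 82.4%.

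**Step 5: the proposed list.** With the last two homes as a block of two, b = 2 and P(5:3 after eight) = 0.

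**The case against.** **The article does not show that the flaw is live.** Block sizes are unstated. A list ending in a block of two would give zero chance of 5:3, and a trials unit might well keep such a restriction out of print. This stands as a limit: the article's silence cannot prove that the list lacks it. But the article states a rule and claims a property for it, and joint release with random block sizes does not have that property.

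**Timing.** A reader might infer that the last two homes are given away before their residents are recruited. The documents support only that it happens before those homes are randomised; nothing says how far recruitment at homes 9 and 10 had gone when the eighth allocation was released. Trial status reports site selection complete with nine homes randomised, and recruitment and randomisation still to finish. That suggests recruitment of residents at the tenth home may have been open, but says nothing about the ninth. The safeguard's stated aim does presuppose that recruitment could still be under way.

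**Pathway to bias.** The unblinded members' described tasks are arranging training, telling managers the allocation and booking follow-up visits. Care home staff identify eligible residents, all eligible residents are to be approached, and reasons for ineligibility are recorded. Anonymous PAM-RC and FAC data on every resident are collected to check representativeness. These points stand and limit both the likely bias and its chance of going unnoticed. The article neither gives the unblinded members a part in choosing homes, units or residents nor excludes one.

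**Blinded researchers.** A reader might infer that they too would assemble the tally from return visits. The article says only "Maintenance of blinding will be monitored and reported by researchers as soon as they become aware of a care home’s allocation". That is a monitoring provision; it does not show that they would learn enough allocations to deduce the rest.

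**Size.** A single balanced list of 10 would give 2 × C(8,3)/C(10,5) = 112/252 = 44%, but that fits poorly with randomly selected block sizes, so I do not rely on it.

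**Conclusion.** The claim that joint release avoids predictability is stated too broadly. It holds for a 4:4 split of the first eight homes and fails for 5:3. For the assumed block sets closing at 10, the chance of failure is about 16% to 37%, and 0% if the final block has size two. If the list is merely cut off at 10, the chance is about 10% to 28%, and after 5:3 the last two allocations follow with probability 81% to 100%, so for some block sets they are likely but not certain.

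A reader might infer that the trial's comparison is biased. The documents do not support that. Bias needs the 5:3 split, recruitment still open at the last homes, and unblinded members able to influence it; none of these is established. The comparison is also described as preliminary and non-definitive. The point merits correction because the fix is cheap and a definitive trial could inherit the rule.

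**What to change.** For list generation, here if still possible and otherwise in the definitive trial, use one of two options:

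1. The CTRU builds the list so that the last two homes form their own block of two, known only to its statistical team, and releases that block only after both homes have completed consent and baseline. Cost: a change to list generation and a sentence of wording, with no extra homes or visits. Downside: the first eight are then always 4:4, so seven disclosed allocations (4:3) would reveal the eighth to anyone who knew of the reserved block.
2. Withhold the eighth allocation as well until homes 9 and 10 have completed consent and baseline. Cost: if home eight is allocated SCTP, its training starts later. A small gap remains: a 5:2 split after seven would fix the last three homes, with probability 0% (sizes 2 and 4), 3% (2, 4 and 6) or 5% (4 and 6) for lists closing at 10.

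If randomisation is already complete, qualify the statement that predictability was avoided, report the split after eight homes, and compare resident recruitment at the last two homes with the other eight using the screening, PAM-RC and FAC data already collected. If the list did end in a block of two, one sentence saying so settles the matter.
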